### Statistical analysis

Firstly, a series of ANCOVAs will be used to test for differences between TPD1 and TPD2 scores on Time 2 perceived ratings of e-cigarette i) harm, ii) addictiveness, iii) social acceptability, iv) effectiveness, v) intentions to purchase and vi) intention to use. We will control for Time 1 measurements of the dependent variable (DV) in each analysis (thus testing differences between TPD1 and TPD2 conditions, controlling for baseline differences).

If no differences between TPD1 and TPD2 are observed, we will collapse these two conditions. The subsequent analysis will use a series of ANCOVAs with 3 between-factors Smoking status (Smoker vs. non-smoker), TPD presence (Present vs. Absent), COMP presence (Present vs. Absent). Dependent variables (DV) will consist of Time 2 perceived ratings of e-cigarette i) harm, ii) addictiveness, iii) social acceptability, iv) effectiveness, v) intention to quit, vi) intention to purchase and vii) intention to use e-cigarettes. We will control for Time 1 measurements of the DV in each analysis (thus testing for change over time, controlling for baseline differences). All main and interactive simple effects will be tested, and we also specifically plan a-priori comparisons between the TPD/no COMP conditions against i) no TPD/no COMP, ii) TPD/COMP, iii) no TPD/COMP, and COMP alone with i) no TPD/no COMP, ii) TPD + COMP, iii) TPD/no COMP. These will be conducted at each level of smoking status.

In addition, the same ANCOVAs will be repeated with the same IVs, DVs and covariates, but additionally controlling for cigarette dependence, previous e-cigarette exposure, and baseline intentions to quit. If differences between TPD1 and TPD2 are observed, we will conduct the above analyses, with TPD presence being expanded to have 3 levels (TPD1 vs. TPD2 vs. No-TPD). The a-priori comparisons will be conducted twice as described above, once with TPD being replaced by TPD1 and the second time with TPD being replaced by TPD2.

Exploratory analyses will be run on each of the variables to check for data distribution, outliers and the type of analysis required. Outliers will be considered on a case-by-case basis and discarded after verification. Analyses will be run using ‘Exclude cases pairwise’ so cases with missing data will not be included in the analysis. Demographics (age, occupation and highest qualification) may be related to perceptions of e-cigarettes as well as intentions to purchase and use e-cigarettes, and quit intentions, so we will explore the relationships between demographic variables and the aforementioned outcome variables.

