## Method

### Design

An experimental, randomised design will be used, with Smoking status (Smoker vs. Non-smoker), TPD presence (TPD1 vs. TPD2 vs. No-TPD; see below) and COMP presence (Presence vs. Absence) as between subjects independent variables, and Time (pre-post exposure of images/health messages) as a within subjects factor. Dependent variables comprise self-reported perceived harm, addictiveness, social acceptability, effectiveness, intentions to purchase and use of e-cigarettes. Smoking dependence, previous e-cigarette exposure, and baseline intentions to quit will be measured as covariates. For the E-cigarette Health Message factor, participants will be exposed to one of the six stimuli versions (see below). Messages will be displayed on e-cigarette packages as per the current EU-TPD warning labels on e-cigarette products. Warning label stimuli are:TPD1: TPD health warning as per currently implemented in the UK. “*This product contains nicotine which is a highly addictive substance*”TPD2: TPD longer health warning as currently implemented in many EU countries: “*This product contains nicotine which is a highly addictive substance. It is not recommended for non-smokers*”COMP: Comparative health message as generated in the pilot study (using the same parameters used for the TPD warning labels; font, font colour, size and placement on the pack)TPD1+: The TPD health warning (TPD1) in combination with the comparative message (using the same parameters above)TPD2+: The TPD longer health warning (TPD2) in combination with the comparative message (using the same parameters as above).No message: A no message condition using the same e-cigarette packages

The primary outcome variables for this study will be smokers’ and non-smokers’ perceptions of e-cigarettes associated with i) harm, ii) addictiveness, iii) social acceptability, iv) effectiveness, v) intentions to purchase, and vi) intentions to use e-cigarettes. Key outcome variables specifically for smokers will be intentions (i) to quit and (ii) use e-cigarettes in a quit attempt. All measures will be taken before and after exposure to messages.

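### TPD1 and TPD2 are pooled when six difference tests find nothing, with no equivalence criterion, no trigger rule for mixed results, no named smoking-status factor and no test of quit intention

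*Protocol article*

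**What the plan says.** The Design section of the protocol article gives the TPD factor three levels. TPD1 is the warning used in the UK. The other version is described as "TPD2: TPD longer health warning as currently implemented in many EU countries"; it repeats TPD1 and adds one sentence advising against use by non-smokers.

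The Statistical analysis section then sets a preliminary step: "a series of ANCOVAs will be used to test for differences between TPD1 and TPD2 scores" at Time 2, adjusting for the Time 1 value of the same outcome. The six outcomes are harm and addictiveness, followed by "iii) social acceptability, iv) effectiveness, v) intentions to purchase and vi) intention to use". The decision rule is: "If no differences between TPD1 and TPD2 are observed, we will collapse these two conditions". After pooling, the model has smoking status, TPD (present or absent) and COMP (present or absent) as factors. If differences are seen, TPD keeps three levels and the planned comparisons are run once for each version.

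The outcome list of the main model has seven entries. It ends "v) intention to quit, vi) intention to purchase and vii) intention to use e-cigarettes", so intention to quit appears there but not in the pretest. The planned comparisons are made separately in smokers and non-smokers.

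**The concern.** There are four weaknesses in the rule as written.

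- **Non-significance stands in for equivalence.** There is no margin and no criterion on a confidence interval, so a real but modest difference can be pooled away.
- **The trigger is undefined.** With six outcomes tested, the text does not say whether one difference keeps three levels for every outcome or only for that one. Two analysts following the article could fit different main models.
- **The pretest averages over smoking status.** The factor is named for the later models but not for this step. The content that separates TPD2 from TPD1 concerns non-smokers, so a different effect by smoking status is plausible, and it is within smoking status that the planned comparisons are made.
- **Intention to quit, the H3 outcome, is pooled with no check.**

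At stake is the interpretation of the TPD effect. The Objectives aim to describe the warnings as implemented. If the UK and the longer EU wording act differently, in general or in one smoking group, a pooled arm describes neither, and the article provides no three-level analysis once pooling has occurred.

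**Working it through.** **The plan's own figure.** The article gives no power or margin for the TPD1 v TPD2 step. Its only power figure is a detectable F of 0.12 at N = 1200, with no alpha, power or degrees of freedom. At alpha 0.05 and 80% power (assumed), the detectable f at N = 1200 is 0.081 (1 df), 0.090 (2 df), 0.104 (5 df) and 0.119 (11 df). So 0.12 is approached only under particular assumed settings, and it says nothing about the pretest.

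**Inputs from the article.** There are 2400 participants (1200 smokers, 1200 non-smokers) in six equal conditions. That is 2400/6 = 400 per condition, or 1200/6 = 200 per condition within each smoking group. If the versions combined with COMP enter the pretest, which the article does not say, there are 800 per TPD version.

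**Assumptions.** Tests are two-sided at 5%. The pre-post correlation r is 0, 0.5 or 0.7, so the ANCOVA residual SD is √(1 − r²) in SD units. The correlation between outcomes is 0, 0.5 or 0.7. Effect sizes are illustrative.

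**1. Missing a true 0.15 SD difference on one outcome.** z = 0.15 / [√(1 − r²) × √(2/n)], and the miss rate is the chance that the test is not significant.

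| n per version | r = 0 | r = 0.5 | r = 0.7 |
|---|---|---|---|
| 400 | z = 2.12, 44% | z = 2.45, 31% | z = 2.97, 16% |
| 800 | z = 3.00, 15% | z = 3.46, 7% | z = 4.20, 1% |

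For 0.1 SD at 400 per version the miss rates are 71%, 63% and 49%. For 0.2 SD they are 19%, 10% and 2%.

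**2. Chance triggering of the three-level model, if any one of six results suffices.** For independent outcomes this is 1 − 0.95⁶ = 0.265. Simulation of six correlated test statistics gives 0.21 (correlation 0.5) and 0.16 (correlation 0.7). With no true difference the arms are therefore pooled about 74%, 79% or 84% of the time.

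**3. Opposite effects: +0.2 SD in one smoking group, −0.2 SD in the other.** The average over equal groups is (0.2 − 0.2)/2 = 0. A test without smoking status then rejects at about its null rate of 5% per outcome. Over six outcomes the arms are pooled about 74% to 84% of the time, just as with no difference at all.

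A test of TPD version by smoking status on the same 400 per version targets 0.2 − (−0.2) = 0.4, with standard error √(1 − r²) × √(4/200). This gives z = 2.83, 3.27 and 3.96, and power of 81%, 90% and 98% for r = 0, 0.5 and 0.7.

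**4. Precision of the alternative.** Within a smoking group, with residual variance σ²:

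- Average of TPD1 and TPD2 against a single condition (control or COMP alone): σ²[¼(1/200 + 1/200) + 1/200] = 0.0075σ². After pooling, 400 v 200: σ²(1/400 + 1/200) = 0.0075σ².
- Average of TPD1 and TPD2 against the average of TPD1+ and TPD2+: σ²[4 × ¼ × 1/200] = 0.005σ². After pooling, 400 v 400: σ²(2/400) = 0.005σ².

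The averaged contrast loses nothing.

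**The case against.** The strongest reply is that the rule does limited harm. Both branches are published in advance. TPD1 v TPD2 is analysed directly on six outcomes whichever branch is taken. A chance trigger merely leads to the three-level model, which is the safer one. H1 to H3 speak of TPD warnings without separating versions, and with equal arms the average of TPD1 and TPD2 is the same quantity that pooling estimates. The pretest also has good power for a same-direction difference of 0.2 SD: 81% to 98% at 400 per version. All of this stands, and it limits the severity.

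Several stronger readings are tempting, and the article does not support them.

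- **That a 0.15 SD difference is pooled 44% of the time.** That rate is for one outcome, takes r = 0 although the ANCOVA adjusts for Time 1, and leaves out the COMP versions. If any of six results is enough to prevent pooling, a difference on several outcomes is pooled less often.
- **That opposite effects are pooled 95% of the time.** That is also a single-outcome rate; over six outcomes it is about 74% to 84%.
- **That pooling gains nothing.** This is true of the averaged contrast. Omnibus TPD main-effect and interaction tests do go from 2 df to 1 df, however (detectable f 0.090 against 0.081 at N = 1200).
- **That the later tests would be misreported.** Nothing in the article says the pretest will go unreported.
- **That smoking status is excluded from the pretest.** The article does not name it there, but does not rule it out. Nor does it predict a reversal of sign between the groups.

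**Conclusion.** The point holds as a should-fix. The article itself states the decision rule, so this is not detail left to an analysis plan. Three defects are visible in the text and need no assumption: there is no equivalence criterion, no rule for mixed results across the six outcomes, and intention to quit is pooled without a test. The fourth, blindness to opposite effects, follows if the pretest is run as described, without smoking status.

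The sizes depend on the assumed alpha, correlations and effects. A 0.15 SD difference on one outcome is missed from 1% to 44% of the time across the cases considered. The equivalence problem therefore concerns small differences, or differences that vary with smoking status. Large differences in the same direction would usually be found.

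Randomisation, data collection and inference on the averaged TPD effect are not impaired. What a change would bring is a model fixed in advance and visible estimates of TPD1 minus TPD2 in each smoking group.

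**What to change.** Remove the pretest and its pooling rule, and always fit TPD with three levels (TPD1, TPD2, No-TPD) alongside COMP and smoking status. Test H1 to H3 with a pre-set contrast of the average of TPD1 and TPD2 against each comparator. Where the comparator is the combined message, use the average of TPD1+ and TPD2+. Report TPD1 minus TPD2 by smoking status with a confidence interval for every outcome, including quit intention in smokers only.

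The cost is a change of analysis wording. No participants or measurements are added, and the averaged contrast is as precise as the pooled one. The small downside is that omnibus TPD main-effect and interaction tests use 2 df instead of 1; testing the hypotheses with the pre-set contrast avoids it.

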The study presents some potential challenges. Previous research suggests that it is important that health messages are clear, comprehensible and credible to increase level of attention and likelihood of recall specifically for individuals with low literacy [5]. A pilot study is currently underway to help develop the most effective comparative message. In a two-stage process, a number of messages were created by the research team and/or extracted from the literature based on the relative risks of e-cigarettes compared to cigarettes. These were then evaluated for accuracy, clarity and persuasiveness by seven experts in the field. Friedman tests were conducted to select the top eight performing messages which will then be evaluated further in a general population sample in a pilot study (*n* = 1000). These messages will be rated on comprehensibility, credibility, and convincingness in order to increase the reach and accessibility of the comparative health message which will be used in the current study. A second potential challenge may be that the aims of the study become clear to participants. In order to minimise this, unrelated filler questions (as described above) will be added following exposure to the stimuli to distract participants from possibly guessing the aims of the study.

Health warnings, such as those implemented by the TPD, may inadvertently deter smokers from initiating use and substituting their tobacco use for e-cigarettes use if their content is deemed too negative. This may be damaging for smokers given that e-cigarettes have been suggested as useful tools to prevent relapse [33, 53]. Conversely, it is possible that our comparative harm message, particularly when delivered alone, may encourage non-smokers to use an e-cigarette. We will therefore fully debrief our participants at the end of the study by presenting accurate information about e-cigarettes, highlighting that the products are not recommended for non-smokers but constitute a less harmful alternative for smokers and that some smokers have found them helpful for quitting smoking.

We hope that our study will allow us to identify the most effective message or combination of messages that will discourage e-cigarette use among non-smokers whilst encouraging use among smokers. Findings of this study have clear relevance for the public health as they will be beneficial in furthering our understanding of how best to communicate relative health risks associated with e-cigarettes.

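### The a-priori contrast list enters TPD alone versus COMP alone twice and never compares TPD+COMP with the no-message control

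*Protocol article*

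**What the plan says.** All references are to the protocol article.

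- **Statistical analysis, first half of the list.** The planned comparisons set "the TPD/no COMP conditions against i) no TPD/no COMP, ii) TPD/COMP, iii) no TPD/COMP".
- **Statistical analysis, second half.** They then compare "COMP alone with i) no TPD/no COMP, ii) TPD + COMP, iii) TPD/no COMP".
- **Strata.** "These will be conducted at each level of smoking status".
- **Other tests.** The same section also commits to testing every main effect and simple effect. If TPD1 and TPD2 turn out to differ, the list is run once with each in place of TPD.
- **Aim (Discussion).** The investigators hope to "identify the most effective message or combination of messages" that discourages use among non-smokers and encourages it among smokers.
- **Outcomes (Design).** "The primary outcome variables for this study will be smokers’ and non-smokers’ perceptions of e-cigarettes", followed by six items: harm, addictiveness, social acceptability, effectiveness, intention to purchase and intention to use. They are not ranked. Quit intention is named separately as a key outcome for smokers.
- **Hypotheses.** H1 concerns harm and addictiveness, H2 intentions to purchase and use, and H3 quit intention in smokers.

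**The concern.** The list looks as if it was meant to cover every pair of the four cells, but one pair is entered from both sides and one is left out. The omitted pair sets the combined label against no message, so the combination is the only message cell without a planned comparison with control.

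TPD alone versus TPD+COMP shows whether the comparative message softens the effect of the warning. It does not show whether the message offsets that effect fully. Nor does it show whether the combined label moves non-smokers' intentions above what they would be with no message. The Discussion itself raises the possibility that the comparative message could encourage non-smokers, particularly when shown alone.

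**Working it through.** **1. Enumerate the pairs.** Write 0 = no message, T = TPD alone, C = COMP alone, TC = both.

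| Entry | First half | Second half |
|---|---|---|
| i | T vs 0 | C vs 0 |
| ii | T vs TC | C vs TC |
| iii | T vs C | C vs T |

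The number of possible pairs is 4 × 3 / 2 = 6. The two entries iii are the same test, so there are 5 distinct pairs. The absent pair is TC vs 0.

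**2. Do the factorial effects supply it?** The simple effects of TPD are T − 0 and TC − C. Those of COMP are C − 0 and TC − T. Each holds one factor fixed. TC − 0 changes both and is none of these. The interaction is (TC − C) − (T − 0), which is also a different quantity.

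**3. Three-level version.** Running the list twice gives 12 entries. T1 vs C, T2 vs C and C vs 0 each appear twice, so 12 − 3 = 9 are distinct. Neither TPD1+ vs 0 nor TPD2+ vs 0 is among them.

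**4. Precision of the missing contrast.** There are 1200 participants per smoking level in six equal conditions, so 1200 / 6 = 200 per condition. After collapsing, TC has 400 and control 200.

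- Collapsed: SE = √(1/400 + 1/200) = 0.087 SD.
- Three-level version: SE = √(1/200 + 1/200) = 0.100 SD.

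Both are before any reduction from adjusting for the Time 1 score.

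**5. The plan's own effect size.** The sample size section gives a detectable F = 0.12 at N = 1200 but no alpha, power or degrees of freedom, so it cannot be reproduced uniquely. Numerator df 3, alpha 0.05 and 95% power give f = 0.120. At alpha 0.05 and 80% power, f would be 0.081 (df 1) to 0.104 (df 5). The stated value is attainable and serves here only as a scale. Assuming d = 2f for a two-group contrast, d = 0.24.

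**6. Cost of an adjustment, if one is used.** H1 and H2 each hold 2 outcomes × 3 comparators × 2 smoking levels = 12 tests. The Bonferroni bound is 0.05/12, with two-sided z = 2.865. Power ≈ Φ(d/SE − z). Besides d = 0.24, take the protocol's odds ratios of 0.52 and 0.41 converted by |ln OR|/1.81, which gives d = 0.361 and 0.493.

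| d | Groups | Power at 0.05 | Power at 0.05/12 |
|---|---|---|---|
| 0.24 | 200 vs 200 | Φ(2.40 − 1.96) = 67% | Φ(2.40 − 2.865) = 32% |
| 0.24 | 400 vs 200 | Φ(2.77 − 1.96) = 79% | Φ(2.77 − 2.865) = 46% |
| 0.36 | 200 vs 200 | 95% | Φ(3.61 − 2.865) = 77% |
| 0.36 | 400 vs 200 | 99% | Φ(4.17 − 2.865) = 90% |
| 0.49 | either | above 99% | about 98% or higher |

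**7. Outcomes against hypotheses.** Of the six primary outcomes, harm and addictiveness match H1, and purchase and use match H2. Social acceptability and effectiveness match no hypothesis. Quit intention (H3) is not among the six, although it enters the main ANCOVAs.

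**The case against.** **The listed contrasts already serve the hypotheses.** H1 and H2 set TPD alone against the other three cells, which is the first half of the list. The attenuation in H3 is T vs TC or the interaction. The aim restated at the start of the Discussion compares the warning as it stands with the warning plus the comparative message, and also considers that message alone. This stands. A reader might infer that TC vs 0 is the policy question and that the trial cannot answer its main question without it. The documents do not support that: the Background describes the warning as mandatory, and no hypothesis depends on the contrast. What is missing is narrower, namely a direct test of the combination against no message.

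**The duplicate does no harm.** Two reference cells, each set against the other three, must share one pair. The same test is read twice with the same result, and it adds no error. This stands too.

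**The difference can be recovered.** TC − 0 = (TC − C) + (C − 0), both of which are listed. That gives a point estimate. It does not give a pre-planned test or interval, because the two pieces share the C cell and their standard errors cannot simply be combined.

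**Error control.** Counting 5 contrasts × 6 outcomes × 2 smoking levels gives 60 tests, and a reader might infer that a false claim is nearly certain. Simulation with shared cells puts the chance of at least one p < 0.05 at 91% with uncorrelated outcomes, about 74% at correlation 0.7 and 57% at 0.9. Those figures assume 5% per test, all 60 nulls true and any single hit being claimed. The article states no alpha and says that smoker/non-smoker differences for H1 and H2 will only be explored. An adjustment may sit in an analysis plan that is not shown, so its absence here is not a finding.

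**Conclusion.** The point holds in limited form. The duplicate entry and the omission of TPD+COMP versus no message are certain from the text and rest on no assumption. The omission leaves H1 to H3 intact. It does leave the aim of identifying the best combination without a direct test of that combination against control, in either the collapsed or the three-level analysis.

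The secondary point also rests on the text alone: six primary outcomes are fixed without ranking, and they do not line up with the hypotheses. In fairness, social acceptability appears in the Objectives and effectiveness in the Discussion's aims, so both are legitimate outcomes. The issue is their confirmatory status, not their inclusion.

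The standard error of 0.087 SD assumes the planned equal allocation and no dropout. The power figures also assume d = 2f, the odds-ratio conversion shown and a normal approximation without ANCOVA gain.

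**What to change.** 1. **Contrast list.** Replace the second TPD-versus-COMP entry with TPD+COMP versus no TPD/no COMP, at each smoking level. In the three-level version, add TPD1+ and TPD2+ versus control. This changes wording only and needs no new data. As a single two-sided 5% test at d = 0.24, it has about 79% power when collapsed (400 vs 200) and 67% in the three-level version (200 vs 200).
2. **Status of the new contrast.** It lies outside H1 to H3, so say whether it is a pre-planned secondary comparison reported with a confidence interval or part of a confirmatory family.
3. **Outcomes.** Name as confirmatory those in H1 (harm, addictiveness), H2 (purchase, use) and H3 (quit intention, smokers only). Report social acceptability, effectiveness and the remaining contrasts as secondary with confidence intervals.
4. **If a multiplicity adjustment is added,** state its cost at the protocol's own F = 0.12 as well as at d = 0.36 and 0.49. At the larger values the loss is modest. At d = 0.24 it is heavy: at the 0.05/12 bound, power falls to about 32% (200 vs 200) or 46% (400 vs 200). A step-down method such as Holm would do no worse than this bound. Applied separately within each hypothesis, it does not control error across all three.

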### Study population/ sample size

The sample will include 2400 participants (*N* = 1200 smokers; N = 1200 non-smokers) all residents in the UK. Given an effect size of between OR = 0.41 and 0.52 (the effect sizes observed in intent to purchase e-cigarettes between control, ingredient and industry warnings respectively) [44] and converting the OR to effect size F using Chinn [45] methodology (Fs = 0.41–0.52) suggest the current study design will need to be powered to detect medium to large effects. The proposed sample (*N* = 1200) allows for detection of small (F = 0.12) main effects and interactions.

Smokers will be matched to the target population of smokers’ demographics in the general population using ONS data by deriving best estimates of required numbers in each condition required at levels of age (banded into two segments), gender (two segments) and Socio-Economic Status (SES) (four segments). The latter will be derived from the number of participants required in the four SES segments (managerial and professional occupations; intermediate occupations; routine and manual occupations; never worked or unemployed). Thereafter, the number in each of these bands for gender and then age bands will be derived resulting in a target number of each of the 16 combinations. A panel agency (Market Research Focus Group Recruiter (MRFGR, a division of AGENTC Ltd)) will be contracted to recruit and randomise to each of these targets using a set of block lists provided by the research team. The same stratification levels will be used for non-smokers matched to population level statistics.

Block randomisation will be used for allocation of conditions and demographic variables (including smoking status) will be stratified so that the sample of smokers is representative of the target population in line with ONS data. Each participant will be assigned to one of the six conditions to obtain equal group sizes using IBM SPSS.

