#### Outcome variables

Prior to, and following the experimental exposure to one of the e-cigarette health messages described above (each presented for a standardised period of 30 s), perceptions of e-cigarettes and intentions will be measured on the following scales: i) harmfulness, ii) addictiveness and ii) socially acceptable, iv) effectiveness as a cessation aid, v) intention to use, vi) intention to purchase and, for smokers only, vii) intentions to quit and use e-cigarettes in a future quit attempt (all on a 7-point rating scales with the anchors “Extremely, to Not at all” scored from 7 to 1; see Table 1 for the full list of constructs). In order to minimise response bias, unrelated (filler) questions will be presented following exposure of the message stimuli in addition to the aforementioned outcome measures. Examples of such questions will include the following: “Which e-cigarette did you find the most appealing?”; “Which e-cigarette (if any) would you be most likely to use?”; “Which e-cigarette did you think looked most like a cigarette?”. Participants will also be asked: “Did you notice a health message on the e-cigarette pack?”; “Did you think the health message was positive, negative, neutral?”

**Table 1 Tab1:** List of constructs (outcome measures)

Constructs	Statements	Anchors
Perceptions of e-cigarettes	How harmful do you think e-cigarettes are?	☐ Extremely (…) ☐ Not at all
	How addictive do you think e-cigarettes are?	☐ Extremely (…) ☐ Not at all
	How socially acceptable do you think e-cigarettes are?	☐ Extremely (…) ☐ Not at all
	How effective do you believe e-cigarettes to be as a quit aid	☐ Extremely (…) ☐ Not at all
Intentions	How likely are you to use an e-cigarette	
	a) in the next month b) in the next 6 months	☐ Extremely (…) ☐ Not at all ☐ Extremely (…) ☐ Not at all
	How likely are you to purchase an e-cigarette	
	a) in the next month b) in the next 6 months	☐ Extremely (…) ☐ Not at all ☐ Extremely (…) ☐ Not at all
	For smokers only	
	How likely is it that you will make a quit attempt:	
	a) in the next month b) in the next 6 months	☐ Extremely (…) ☐ Not at all ☐ Extremely (…) ☐ Not at all
	How likely are you to use an e-cigarette in a quit attempt	
	a) in the next month b) in the next 6 months	☐ Extremely (…) ☐ Not at all ☐ Extremely (…) ☐ Not at all

Note: Each of these statements will be presented prior to and following exposure to one of the e-cigarette health messages

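### The outlier sentence permits valid 1–7 ratings to be discarded after randomisation, which can bias the non-smoker intention contrasts toward no effect

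*Protocol article*

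**What the plan says.** The Statistical analysis section of the protocol article opens its data-screening paragraph with "Exploratory analyses will be run on each of the variables to check for data distribution, outliers and the type of analysis required". It then says "Outliers will be considered on a case-by-case basis and discarded after verification". The next sentence excludes cases pairwise, "so cases with missing data will not be included in the analysis", so a discarded rating takes that participant out of the analysis concerned.

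Under Outcome variables, the perception and intention items are "all on a 7-point rating scales with the anchors" running from extremely to not at all, scored 7 to 1. They are answered online.

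The main models are ANCOVAs of the Time 2 rating: "We will control for Time 1 measurements of the DV in each analysis". The planned comparisons include COMP alone against the condition with neither message, and "These will be conducted at each level of smoking status". A contrast within non-smokers is therefore part of the plan. The Discussion accepts that the comparative message, above all when shown alone, "may encourage non-smokers to use an e-cigarette".

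**The concern.** The sentence commits to an action, discarding, and leaves its trigger to judgement. For a variable such as age, an extreme value may be an entry error. For a closed 7-point opinion item it cannot be recognised as one from its size: 7 is as admissible as 1, and no source record exists against which an opinion could be checked.

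Non-smokers in this study are never-smokers, and exclusive vapers, dual users and former smokers are excluded. Ratings of intention to use or buy that pile up at 1 are therefore plausible. In such a distribution the only values that can look extreme are the high ones. If a message raises intention in some non-smokers, its condition holds more of those values and loses more of them. The contrast then moves toward no effect, which is the reassuring direction for a question the article itself raises.

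**Working it through.** **No figure to reproduce.** The article gives no outlier criterion, rating distribution or expected loss. Its one design figure, F = 0.12, does not enter this point.

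**Inputs from the article.** Ratings run from 1 to 7. There are "N = 1200 non-smokers" in six equal conditions, so 1200 / 6 = 200 per condition.

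**Assumptions.** The distributions below, the outlier rules, and a two-sided 5% test are all assumed. Percentages are for scores 1 to 7 in non-smokers.

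| | Control | COMP alone |
|---|---|---|
| A | 70, 12, 7, 5, 3, 2, 1 | 64, 13, 8, 6, 4.5, 3, 1.5 |
| B | 85, 6, 3, 2, 2, 1, 1 | 80, 7, 4, 3, 3, 1.5, 1.5 |
| C | 92, 3, 2, 1, 1, 0.5, 0.5 | 88, 4, 2.5, 2, 1.5, 1, 1 |
| D (shift from 1 to 5 or 6) | 85, 8, 3, 2, 1, 0.5, 0.5 | 81, 8, 3, 2, 3, 2.5, 0.5 |
| E (shift from 1 to 2–4) | as D | 77, 12, 6, 3, 1, 0.5, 0.5 |

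**Formulas.** Pool the two conditions. With pooled proportions p, m = Σ x·p, s = √Σ p(x − m)², and the cut is m + 3s. The mean after discarding is Σ x·p / Σ p over x ≤ cut, within each condition. Loss = 1 − (difference after / difference before). Power ≈ Φ(z − 1.96) + Φ(−z − 1.96), with z = difference / (SD·√(2/200)), where SD is the root mean square of the two within-condition SDs. Power is unadjusted for Time 1, and n is not reduced for removed cases.

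**3-SD flag computed within non-smokers**

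| | m | s | Cut | Removed, control / COMP | Difference before → after | Loss | Power before → after |
|---|---|---|---|---|---|---|---|
| A | 1.790 | 1.404 | 6.00 | 1.0% / 1.5% | 0.200 → 0.176 | 12% | 0.30 → 0.28 |
| B | 1.448 | 1.180 | 4.99 | 4.0% / 6.0% | 0.155 → 0.068 | 56% | 0.26 → 0.19 |
| C | 1.258 | 0.923 | 4.03 | 2.0% / 3.5% | 0.125 → 0.0534 | 57% | 0.27 → 0.19 |
| D | 1.385 | 1.052 | 4.54 | 2.0% / 6.0% | 0.180 → 0.009 | 95% | 0.40 → 0.05 |
| E | 1.360 | 0.917 | 4.11 | 2.0% / 2.0% | 0.130 → 0.133 | none | 0.30 → 0.52 |

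In every row m − 3s is below 1, so no low rating can be flagged.

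D worked through: the control mean is 1.295 before and (1.295 − 0.050 − 0.030 − 0.035) / 0.98 = 1.204 after. The COMP mean is 1.475 before and (1.475 − 0.150 − 0.150 − 0.035) / 0.94 = 1.213 after.

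**Box-plot rule (Q3 + 1.5 IQR) within non-smokers.** In B and C both quartiles equal 1, so the IQR is 0 and every answer above 1 is flagged: 15% against 20% in B, 8% against 12% in C. The difference falls to 0. In A, Q3 = 2 and the cut is 3.5. The rule removes 11% against 15%, and the difference falls from 0.200 to 1.14/0.85 − 1.15/0.89 = 0.049, a loss of 75%.

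**3-SD flag on smokers and non-smokers together.** Combine D with an equal number of smokers whose ratings are spread out (assumed mean 3.42, SD 1.92). Then m = 2.405, s = 1.856 and the cut is 7.97. Nothing can be flagged and 0.180 stands. If smokers scored low enough to bring the cut between 5 and 6, only 6s and 7s would go. The difference would be 1.29/0.97 − 1.23/0.99 = 0.087, a loss of 51%.

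**Smokers alone.** With the same spread-out ratings the cut is about 9.2, so nothing is removed.

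**The case against.** The strongest reply is that verification is there to establish error: on an ordinary reading, a value goes only once it is confirmed to be wrong. The sentence also covers variables where wrong entries do occur, and even on a closed item a check may expose inattentive responding in a paid panel. That reading is possible, but the text does not state it. As written, it makes discarding the outcome for whatever is called an outlier. The reply does show that discarding is not wrong for every variable.

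A second reply is that a condensed article may leave the criterion, the verification procedure and the masking to a fuller document. This is right as far as it goes, and their absence is not the point. The point is the stated disposition, applied to outcomes for which an extreme in-range value is no evidence of error.

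A third reply is that the large losses are built into the examples. That is true of D, where the whole shift is placed above the cut. E, with the shift confined to low scores, loses nothing and gains power. A flag computed on both smoking groups together may remove nothing.

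A reader might also infer that the decisions will be taken with condition known, or that the study is built to detect uptake in non-smokers. The article is silent on masking. Its Discussion states no a priori prediction for the comparative message in non-smokers, and its hypotheses only explore differences by smoking status.

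**Conclusion.** The point holds in a limited form. The plan permits a discretionary, outcome-dependent exclusion of valid ratings after randomisation. Where non-smokers' ratings cluster at 1 and the flag is computed within non-smokers, it can remove only high ratings and can bias the COMP-versus-control contrast on intention toward no effect.

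The size cannot be fixed from the article. Under the assumed distributions it runs from no loss, through about 12% to 57% of the difference (scenarios A to C, 3 SD), to 75% to 100% under a box-plot rule and 95% in scenario D.

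It would go too far to say that the rule will delete the high-intention answers, or that it removes 95% of the effect. Both need a criterion and a distribution that the article does not give. The concern also need not reach smokers' ratings or perception items that use the middle of the scale. The check uses Time 2 ratings alone and does not model the adjustment for Time 1.

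**What to change.** Replace the outlier sentence with wording such as:

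> All in-range (1–7) outcome ratings of randomised participants are retained in the primary analysis. Only impossible values, duplicates, or records failing data-quality criteria fixed in advance and applied without reference to condition or outcome values are removed. Removals are reported by condition and smoking status.

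Any analysis that leaves out extreme ratings should be labelled a sensitivity analysis. The cost is this change of wording, a short list of data-quality criteria written before the data are seen, and a small table of removals. No change to the ANCOVA follows from this point: robust standard errors or an ordinal model may be considered for skewed ratings, but that is a separate choice.
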